## 2 RATIONALE

---

The ACT PROCESS study proposed here is designed to evaluate the process, context and impact of the intervention implemented in the ACT PRIME study in order to further our understanding about why the HFI was effective, or not. This will be achieved through a comprehensive evaluation framework implemented in parallel with ACT PRIME.

ACT PROCESS consists of four linked evaluation components including: 1) logic model, 2) process evaluation, 3) context evaluation, 4) impact evaluation. The logic model is developed alongside the HFI intervention design stage and aims to detail the components, effects and intended outcomes of the HFI. The logic model informs the development of the data collection tools for the remaining components of the evaluation. The process evaluation will document the process of implementing the HFI including health worker training activities, health center management tools, supply of artemether-lumefantrine (AL) and rapid diagnostic tests (RDTs) for malaria, and interactions with local and district stakeholders from the perspective of implementers, health workers and community members. The context evaluation will capture information on factors that may have affected the HFI implementation or outcomes including other interventions or programmes implemented in the area, changes to malaria case management guidelines, and other environmental, economic, political or individual factors. The impact evaluation will assess the wider impact of the HFI beyond outcomes of ACT PRIME at the household, community, private sector, and public health system levels.

To facilitate our understanding about why the HFI was effective or not, links will be made between the clinical and economic outcomes of the ACT PRIME study and the process, context and impact outcomes of the ACT PROCESS study. This understanding is essential for interpreting and informing the development of a health facility intervention which is sustainable and reproducible by the MoH in Uganda, and elsewhere.

## 3 STUDY OBJECTIVES

---

### 3.1. PRIMARY OBJECTIVE

**To evaluate the process, context and impact of the HFI in the ACT PRIME study in order to further our understanding about why the HFI was effective, or not.**

### 3.2. SECONDARY OBJECTIVES

1. To develop a comprehensive logic model of the ACT PRIME HFI with intervention components mapped through to their intended effects and outcomes.
2. To evaluate the process of the HFI implementation including health worker training, health center management tools, supply of AL and RDTs for malaria, and interactions with local and district stakeholders.
3. To develop a rich contextual record of factors that may have affected the HFI implementation outcomes such as other interventions or programmes implemented in the area, changes to malaria case management guidelines, and other environmental, economic, political or individual factors.
4. To assess the wider expected and unexpected impacts of the HFI at the household, community, private sector, and public health system levels.

## 4 COMPREHENSIVE EVALUATION FRAMEWORK

### 4.1. OVERVIEW

Figure 4.1 illustrates the comprehensive evaluation framework for the study proposed here including the process, context and impact evaluation as they relate to the ACT PRIME study HFIs.

**Figure 4.1 ACT PROCESS study comprehensive evaluation framework**

[figure not shown]

Data for the process, context and impact evaluations will be gathered through self-filled questionnaires, health worker communication assessments, IDIs, FGDs and a structured contextual record as outlined in Table 4.1 and described in Chapter 5.

**Table 4.1 ACT PROCESS Evaluation methods**

| Evaluation method                                                 | Participants                                                                                                    | Evaluation component |                    |                   | Maximum sample size |
|-------------------------------------------------------------------|-----------------------------------------------------------------------------------------------------------------|----------------------|--------------------|-------------------|---------------------|
|                                                                   |                                                                                                                 | Process evaluation   | Context evaluation | Impact evaluation |                     |
| Self-filled questionnaires                                        | 
 
– Trainees
 
– Trainers
 
                                | X                    |                    |                   | 350                 |
| Health worker communication assessments + patient exit interviews | 
 
– Caregivers & children under 5
 
– Health workers
 
 | X                    |                    |                   | 375                 |
| In-depth interviews                                               | – HFI Health workers                                                                                            | X                    | X                  | X                 | 10                  |
|                                                                   | – Implementers                                                                                                  | X                    | X                  | X                 | 5                   |
|                                                                   | – Key stakeholders                                                                                              |                      | X                  | X                 | 10                  |
| Semi-structured questionnaires                                    | – HFI Health workers                                                                                            | X                    | X                  | X                 | 10                  |
|                                                                   | – Standard care health workers                                                                                  | X                    | X                  | X                 | 10                  |
|                                                                   | – Private drug shops                                                                                            |                      | X                  | X                 | 10                  |
| Focus group discussions                                           | – Primary caregivers                                                                                            | X                    | X                  | X                 | 8                   |
|                                                                   | – Community health workers                                                                                      |                      | X                  | X                 | 8                   |
| Structured contextual record                                      | – Completed by study team                                                                                       |                      | X                  |                   | 10                  |

## 4.2. LOGIC MODEL

An initial logic model is illustrated in Figure 4.2. The logic model will be revised to ensure all components of the interventions are accurately mapped through to their intended effects and outcomes. The process of mapping the intervention started during the design phase for the ACT PRIME HFI. The design phase was a consultative process between investigators and implementers using our formative research, input from stakeholders, evidence from the literature, and behaviour change theory. Using these components, the intended mechanism of effect and the source for the hypothesised mechanism was specified. This informed the development of a logic model which describes in detail the proposed HFI components, mechanisms of effect and intended outcomes. This logic model forms the basis of subsequent evaluation components.

**Figure 4.2 Logic model**

[figure not shown]

### 4.3. PROCESS EVALUATION

The process evaluation will involve two lines of research, (1) documentation of the implementation of the intervention as delivered by the study team and (2) qualitative study of the functioning and interpretation of the intervention by implementers and recipients. As outlined in Figure 4.1, we will be evaluating four aspects of the HFI including (1) health worker training modules, (2) health center management tools, (3) supply of AL and RDTs for malaria, and (4) interaction with the district regarding staffing and drug stocks.

#### 4.3.1. Documentation of implementation

The logic model will be used to identify relevant activities for the process evaluation. For each activity, the following evaluation criteria will be used as categories of assessment [37].

- Fidelity (quality)                      The extent to which the intervention was implemented as planned
- Dose delivered (completeness)      Amount or number of intended units of each intervention or component delivered or provided by interventionists
- Dose received (exposure)            Extent to which participants actively engage with, interact with, are receptive to and/or use materials or recommended resources. Can include 'initial use' and 'continued use'

- Reach (participation rate) Proportion of the intended priority audience that participates in the intervention; often measured by attendance; includes documentation of barriers to participation
- Recruitment Procedures used to approach and attract participants at individual or organizational levels; includes maintenance of participant involvement in intervention
- Context Aspects of the environment that may influence intervention implementation or study outcomes; includes contamination

Variables for data collection for each activity are formulated under each of the above headings by analysing the materials used for the HFI implementation including:

- Training packages: Health center management training; Training in fever case management and use of RDTs, Training in patient-centered services.
- Management tools: PHC Fund Accounting Tool, ACT Drug Distribution Assessment Tool
- Supply of AL and RDTs: drug stock cards, requisition and issue vouchers from health centers and the health sub-district records
- District and health sub-district interactions: Logs documenting interactions with district, health sub-district, and health center staff.

We will capture information on these variables during the implementation and monitoring and evaluation of the HFI using monthly health center records, health worker training evaluation self-filled questionnaires, IDIs with health workers and FGDs with primary caregivers. The data captured will be linked with other quantitative outcome data collected through ACT PRIME using unique identifiers of health center, community or individual health worker or intervention participant.

#### **4.3.2. Assessment of intervention mechanisms**

Perceptions of both recipients and implementers of interventions as the intervention is being rolled-out will be evaluated through the self-filled questionnaires, health worker communication assessments, IDIs and FGDs. Questions will explore the awareness, understanding of purpose, perception of relevance and usefulness, level of adoption and interpretation of importance in practice of each component of the intervention for respondents. All health worker training participants will complete the self-filled questionnaires; all health workers will be invited to participate in the health worker communication assessments; and a cross-section of participants will be invited to the FGDs (primary caregivers) and IDIs (health workers, implementers).

### **4.4. CONTEXT EVALUATION**

Both local and regional/national contextual factors will be documented throughout ACT PRIME using a structured contextual record completed by the study team and rich contextual descriptions gathered through IDIs and FGDs.

#### **4.4.1. Structured contextual record**

The structured contextual record will involve the recording of details about factors that may affect ACT PRIME implementation and impact at three-monthly intervals by the implementing team. A structured record format will be used to document these contextual factors for each health center, and at the district level.

Factors may include the following:

- Other interventions involving malaria at the community level in the trial area
- Other research involving malaria at the community level in the trial area
- Other interventions at the health center level in the trial area
- Other research at the health center level in the trial area
- Other training programmes involving CMDs or health center staff involved in the trial
- Specific personalities or political problems at any communities/health center
- Change of staff at health center
- Change of community medicine distributor or village health team members
- Guideline changes about malaria testing and treatment at health centers/elsewhere
- Messages or news stories about malaria testing on radio/TV/newspapers
- Level of support (low, medium, high) from district health management team for the intervention
- Other local or national economic or political factors that may have impacted the delivery or receipt of this intervention

The source of each item added to the local context document will be noted on the document. The data collected in these tables will be assimilated into a report of concurrent activities and other contextual factors overall. Factors that varied widely will be used in the final analysis of the intervention impact as potential explanatory variables.

#### **4.4.2. Rich description of context**

Rich descriptions of contextual factors will be collected in all IDIs and FGDs in order to identify any contextual factors participants feel may have affected the impact of the intervention.

Representatives from a randomly selected cross-section of health centers and communities will be invited to participate, and district officials will be purposively selected to represent those with most insight into the intervention process.

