### **5.3.3. In-depth interviews**

We will conduct up to 25 IDIs with different target populations including HFI implementers (up to 5 interviews), health workers in the HFI arm (up to 10 interviews), and key local and district stakeholders (up to 10 interviews).

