### **5.3.4. Semi-structured questionnaires**

We will conduct up to 30 interviews to complete semi-structured questionnaires with different target populations including health workers in the HFI arm (up to 10 interviews), health workers in the standard care arm (up to 10 interviews), and private drug shop workers (up to 10 interviews). For the health worker interviews, we will target the in-charges of the health facilities.

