### **5.3.5. Focus group discussions**

We will conduct up to 16 FGDs with primary caregivers and community health workers from the study area selected by convenience sampling.

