## **5.7. SEMI-STRUCTURED QUESTIONNAIRES**

We plan to administer semi-structured questionnaires with health workers from HFI and standard care arms, and private drug shop workers. The purpose of the questionnaires is to collect information on the contextual factors and perceptions of the HFI as it is being implemented as well as the expected and unexpected impacts of the HFI. Written informed consent to conduct the interviews and administer the questionnaires will be obtained from all participants before beginning (Appendix T) as outlined in section 8.2. The interviews with health workers and private drug shop workers will be conducted approximately 9-12 months after the HFI roll-out.

Health workers from HFI and standard care arms will be selected by convenience sampling to ensure at least one health worker from each health facility participates in an interview. We plan to complete up to 10 interviews with health workers in both ACT PRIME arms, 20 in total. The draft questionnaire (Appendix U) will be piloted prior to the onset of the study, and will be refined if necessary.

Private drug shops workers will be randomly selected from the database developed for the Tororo District Survey Project. We plan to complete up to 10 interviews with private drug shop workers. The draft questionnaire (Appendix V) will be piloted prior to the onset of the study, and will be refined if necessary.

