## 5.8. FOCUS GROUP DISCUSSIONS

We plan to conduct FGDs with primary caregivers and community health workers from both the HFI and standard care arms. The purpose of the FGDs is to collect information on the contextual factors and perceptions of the intervention as it is being implemented as well as the expected and unexpected impacts of the HFI on communities in the study area. Written informed consent to conduct the FGDs will be obtained from all participants before beginning (Appendix W), as outlined in section 8.2. Participants for FGDs will be selected from the HFI arm and the standard care arm; the same groups of participants will be invited to attend from each arm. The definition of each target population is provided in Table 5.2.

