**PART 2: IMPLEMENTER IN-DEPTH INTERVIEW (4)**

**Domains, topic questions, and probes:** Use the table below to help you administer the questions during the interview.

| Domain                                                                              | Topic and Probes                                                                                                                                                           |
|--------------------------------------------------------------------------------------------|-----------------------------------------------------------------------------------------------------------------------------------------------------------------------------------|
| 7. Context                                                                          | a) Aside from the HFI, can you describe any other programmes/interventions involving malaria in the area? Probe: is the programme at the community or health centre level? |
|                                                                                            | b) Aside from the HFI, can you describe any other health-related programmes/interventions in the area? Probe: is the programme at the community or health centre level?    |
|                                                                                            | c) Are there any other factors you think may have influenced the delivery or receipt of the ACT PRIME HFI?                                                                        |
| 8. Closing                                                                          | Is there anything else you think is important about the implementation of the HFI intervention that we have not talked about?                                                     |
| 
 
✓ Summarise
 
✓ Thank participant
 
 |                                                                                                                                                                                   |

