|                                                                                                                             | b) Was there anything that you learnt in principle that you have found difficult to put into practice?                                                    |
|                                                                                                                             | c) Have you attended any other training courses or received any materials or tools from other organizations to help you do your job? If yes, please list. |

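### The health-worker questionnaire used in both arms never asks about other programmes or what caused a change, and the caregiver guide has only one probe, although both are assigned to the context evaluation

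*Supplement*

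**What the plan says.** Section 4.4 plans two sources on context: a structured record kept by the study team, and description from participants. For the second, section 4.4.2 states that "Rich descriptions of contextual factors will be collected in all IDIs and FGDs", with the aim of learning what participants themselves think affected the intervention's impact. Table 4.1 marks the context column for every in-depth interview (IDI), SSQ and focus group (FGD) row, including standard-care health workers and primary caregivers.

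Section 5.7 says the SSQ is meant to "collect information on the contextual factors and perceptions of the HFI as it is being implemented". Section 5.8 says the FGDs are meant to "collect information on the contextual factors and perceptions of the intervention as it is being implemented". Secondary objective 3 (section 3.2) names other programmes and guideline changes among the factors to be recorded, and section 4.3.1 counts contamination as part of context.

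Two guides have sections devoted to context. Implementers (Appendix Q, domain 7) are asked about other programmes and "Are there any other factors you think may have influenced the delivery or receipt of the ACT PRIME HFI". Stakeholders (Appendix S, domains 4 and 5) are asked about contextual factors and other programmes. HFI-arm health workers (Appendix R, item 3c) are asked "Have you attended any other training courses or received any materials or tools from other organizations to help you do your job".

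A note on lettering: the caregiver guide carries the heading Appendix Y and the community health worker (CHW) guide Appendix X, but sections 5.8.1, 5.8.2 and 10 give these letters the other way round. The letters on the tools are used here.

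**The concern.** PROCESS exists to explain why PRIME did or did not show an effect. One rival explanation for a small arm difference is that another organisation trained, supplied or staffed the standard-care centres. The people best placed to report this are the staff of those centres. IDIs with health workers are confined to the HFI arm (sections 5.3.3 and 5.6), and the communication assessments are marked in Table 4.1 for process only. Appendix U is therefore the one interview in which PROCESS could put the question to standard-care staff, and it does not. Caregivers, who see what changes at a centre and in the village, are also not asked about other programmes or events. If neither group is asked, their view of competing explanations will be on file only where someone volunteers it.

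**Working it through.** No power or sample-size formula applies. The check is a count of planned contacts and an item-by-item reading of each tool.

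**Planned numbers.** Section 5.3.3: "We will conduct up to 25 IDIs with different target populations". Section 5.3.5: "We will conduct up to 16 FGDs with primary caregivers and community health workers". Section 5.3.4: "We will conduct up to 30 interviews to complete semi-structured questionnaires". The Table 4.1 rows reproduce these totals:

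- IDIs: 10 HFI health workers + 5 implementers + 10 stakeholders = 25
- FGDs: 8 caregiver + 8 CHW = 16
- SSQs: 10 HFI + 10 standard care + 10 drug shops = 30
- IDIs and FGDs together: 25 + 16 = 41

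**What each tool asks.**

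| Tool | Arm | Context content |
|---|---|---|
| App. Q implementers (5) | not arm-specific | Own context domain |
| App. S stakeholders (10) | district | Own context and other-programme domains |
| App. R health workers (10) | HFI only | Item 3c on other organisations' training, materials or tools; staffing changes; probes on why changes occurred |
| App. X CHW groups (8) | both | Training and its provider; reasons for changes in patients and in malaria treatment; drug supply and its supplier |
| App. Y caregiver groups (8) | both | One probe (7a) on what brought change at the nearest centre |
| App. U health workers (10 + 10) | both | No question on other programmes, outside support or cause of change |

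Appendix U, Part 1, Section 1 asks whether patient management changed, which change mattered most, why it matters and what difference it made. It does not ask what brought it about. Sections 2 to 5 cover stock, staffing, PHC funds and patient management without asking whether an outside body was involved. Section 8 is an open comment box that invites remarks on changes that have improved services. Part 2 is for HFI workers only and concerns PRIME's own training and tools. By contrast, the drug-shop questionnaire and the CHW guide do ask respondents for the reason behind a change.

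**Coverage of IDIs and FGDs.**

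- With a dedicated context domain: 5 + 10 = 15 of 41
- With at least one explicit context question: 15 + 10 (App. R) + 8 (App. X) = 33 of 41
- The remaining 41 − 33 = 8 are the caregiver groups, which have the probe only

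**Standard-care arm.** This assumes two CHWs per village (section 5.8.2 calls that typical) and 6 to 12 caregivers per group (section 5.8.1). Drug shops are left out.

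- CHWs: 4 groups × 5 villages × 2 = 40, with explicit questions
- Caregivers: 4 groups × 6 to 12 = 24 to 48, with the probe only
- Health workers on Appendix U: 10, with neither
- Share with an explicit question: 40/(40 + 24 + 10) = 40/74 = 54%, or 40/(40 + 48 + 10) = 40/98 = 41%
- Share if the caregiver probe counts: 64/74 = 86% to 88/98 = 90%

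The remaining 10% to 14% are the health workers.

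**The case against.** The strongest reply is that context does not rest on these tools. The structured record (section 4.4.1, Appendix Z) is completed every three months for each health centre. Its form codes 20 facilities, so both arms face the same items on staff changes, new interventions, training, research, community programmes, policies and guidelines. The centre's in-charge is a coded source for the facility items. Stakeholders are asked whether changes affected all centres or only some. Appendix U Part 1 is identical in both arms, has an open comment box, and is described in section 5.7 as a draft to be piloted. It is also neither an IDI nor an FGD, so the section 4.4.2 sentence does not govern it.

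Much of this stands. A reader who counts guides without a context domain (26 of 41, or 63%) might infer that most tools ignore context, or that almost nobody in the standard-care arm is asked. The documents do not support either inference: that count is of headings, not questions, and the figures in the working show otherwise. Nor do they support the inference that the design as a whole looks for co-intervention harder in one arm. Among the context interviews with health workers, the imbalance is in one item, Appendix R 3c.

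What the reply does not remove is narrower. The record is filled in by the implementing team, and the sources named in section 5.9 are mainly literature, media, official notices and websites; that section describes no interview at each centre. It cannot supply what section 4.4.2 seeks, the participants' own view. The Appendix U gap conflicts with Table 4.1 and section 5.7 even though it does not conflict with section 4.4.2.

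**Conclusion.** The point holds as a limited mismatch between stated purpose and instrument. Up to 10 standard-care health workers have no PROCESS interview question on other programmes, outside support or the cause of change, while up to 10 HFI-arm workers are asked about other organisations' training and tools. All 8 caregiver groups, 4 of them in standard care, have a single attribution probe where section 4.4.2 promises rich description. The HFI health-worker and CHW guides already contain real context questions, and the record covers all 20 facilities, so what is missing is frontline standard-care workers' and caregivers' own accounts. This affects how a PRIME result can be explained; it does not bias the PRIME estimate itself.

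The conclusion rests on the tools as shown. PRIME's own questionnaires are not in the document and might ask some of this. The first page of the drug-shop questionnaire is also not shown and was not judged. Head counts are planned maxima or ranges.

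**What to change.** In Appendix U, Part 1, for both arms, add two questions:

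- 'In the past 12 months has any other organisation or programme provided training, supplies, staff or activities at this centre? Which, and when?' Place it outside Section 1, so that a respondent who reports no change is not skipped past it, and instruct interviewers not to count PRIME itself. With interviews about 9 to 12 months after roll-out, a 12-month window reaches back to roll-out.
- After Section 1, question 2: 'What do you think brought this change about?'

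In the caregiver guide (headed Appendix Y), add one question on other health programmes or events in the area. Additions to Appendices R and X are optional, since both already ask context questions.

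The cost is two questions in a questionnaire still to be piloted and one in a topic guide: a few minutes per respondent, with no new visits and no change in sample.
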